## Abstract

**Background:**

In Australia and internationally, there is concern about the growing proportion of women giving birth by caesarean section. There is evidence of increased risk of placenta accreta and percreta in subsequent pregnancies as well as decreased fertility; and significant resource implications. Randomised controlled trials (RCTs) of continuity of midwifery care have reported reduced caesareans and other interventions in labour, as well as increased maternal satisfaction, with no statistically significant differences in perinatal morbidity or mortality. RCTs conducted in the UK and in Australia have largely measured the effect of *teams *of care providers (commonly 6–12 midwives) with very few testing *caseload *(one-to-one) midwifery care. This study aims to determine whether caseload (one-to-one) midwifery care for women at low risk of medical complications decreases the proportion of women delivering by caesarean section compared with women receiving 'standard' care. This paper presents the trial protocol in detail.

**Methods/design:**

A two-arm RCT design will be used. Women who are identified at low medical risk will be recruited from the antenatal booking clinics of a tertiary women's hospital in Melbourne, Australia. Baseline data will be collected, then women randomised to caseload midwifery or standard low risk care. Women allocated to the caseload intervention will receive antenatal, intrapartum and postpartum care from a designated primary midwife with one or two antenatal visits conducted by a 'back-up' midwife. The midwives will collaborate with obstetricians and other health professionals as necessary. If the woman has an extended labour, or if the primary midwife is unavailable, care will be provided by the back-up midwife. For women allocated to standard care, options include midwifery-led care with varying levels of continuity, junior obstetric care and community based general medical practitioner care. Data will be collected at recruitment (self administered survey) and at 2 and 6 months postpartum by postal survey. Medical/obstetric outcomes will be abstracted from the medical record. The sample size of 2008 was calculated to identify a decrease in caesarean birth from 19 to 14% and detect a range of other significant clinical differences. Comprehensive process and economic evaluations will be conducted.

**Trial registration:**

Australian New Zealand Clinical Trials Registry ACTRN012607000073404.

## Background

Continuity of carer in the provision of maternity care has been strongly recommended and encouraged in Victoria and throughout Australia. The Victorian Department of Human Services (DHS) released a policy document "Future directions for Victoria's maternity services" [1] in June 2004 which endorsed and promoted the expansion of public models of maternity care that offer continuity of *carer*. Many hospitals have responded by introducing caseload midwifery, a one to one midwifery model of care in which women are cared for by a primary midwife throughout pregnancy, birth and the early postnatal period; a model of care that has been subjected to very little rigorous evaluation. We know of only two randomised controlled trials (RCTs) of caseload midwifery care; both conducted in the United Kingdom in the1990s [2,3]. One did *not *include an 'on call' component for midwives [2], whereby midwives are called in to work when a woman in their caseload requires labour care. This aspect is likely to have a significant impact on midwives' lives and has been a common component of the model when implemented in Australia. The other was a cluster trial, with all midwives attached to between one and three general medical practices [3] – a very different system of maternity care than that available in Australia. Other evaluations of the caseload model have used comparative descriptive designs, with most arguing that for feasibility and practical reasons using an RCT design was not possible [4-6]. There have been no RCTs of caseload midwifery care in Australia.

There is evidence from RCTs that continuity of midwifery care may lead to reduced caesarean sections [7,8] and instrumental vaginal births [9], and a decrease in other interventions during labour including induction [3,9] augmentation [9] analgesia use [9] and episiotomy [10,11]. One Australian RCT demonstrated a decrease in women having caesarean birth from 18% to 13% [7]. Many of these RCTs have also reported increased satisfaction for women [11-14], with no statistically significant differences in perinatal morbidity or mortality [9,15]. RCTs of continuity of midwifery care in the UK and in Australia have largely measured the effect of *teams *of care providers (commonly 6–12 midwives). Caseload midwifery care differs in that women are cared for by a *primary *midwife throughout pregnancy, birth and the early postnatal period. The underlying philosophy is one of continuity of carer for both women and midwives. The primary midwife is on call for labour and birth care for the women in her caseload. One or two other midwives are introduced during pregnancy in case they are needed as a back-up, for example if the primary midwife has two women in labour at the same time, if a woman's labour is quite extended or if the primary midwife is on days rostered 'off call' or leave when labour begins. A fulltime midwife usually cares for 40–45 women per year [16].

The impact of the caseload midwifery model on staff retention and attrition is unknown, but is another important issue for consideration in light of the fact that a 2002 review of the midwifery workforce in Australia concluded that there is a national shortage of midwives that is expected to increase over the next few years [17]. It is possible that the continuity inherent in caseload midwifery and potential for lower intervention childbirth would improve midwife satisfaction [18-21]; however studies in the UK and Australia have reported problems with the widespread implementation and organisation of models that promote continuity of carer. Issues for midwives include high and unsustainable workloads, personal costs (impinging on family life) [22,23]; and burnout and stress [24]. A caseload model in Sydney ceased operations in 2001 following "many stressors from within and beyond the partnership model" [[5], p34]. In response to these issues, some organisations have altered their approach, and moved from a caseload model to midwifery teams [25]. A 2000 review of continuity of carer models concluded that services should be organised in a way that aims to put less strain on midwives' lives [26]. Conflict between midwives working in new models and the staff in traditional models has also been reported [27,28]. Midwives in new models, or the new models themselves, may be seen as a threat by medical staff, in that the midwives may be taking on work otherwise done by them [21]. In a qualitative evaluation of a team midwifery model in Brisbane, midwives were surprised by the lack of support from other staff, both peers and administrators [27]. In two other trials it was reported that team midwives had to frequently respond to criticisms about their role or work practices [28]. In a setting of midwifery workforce shortages it is critical that the impact of new models of care is properly evaluated with regard to midwife job satisfaction, recruitment and retention.

There is a lack of evidence regarding the safety and the efficacy of the caseload model, although the existing RCTs of midwifery care (mostly team midwifery) do report decreases in interventions in labour and birth. In Victoria in 2004, 30% of births were by caesarean; a rate that has almost doubled over the past 20 years [29]. Reports in the USA and Australia have shown that the increase is related partly to non-clinical factors such as demographics, physician practice patterns, and maternal choice [30-34]. In Australia, intervention rates are highest among women with private health insurance, women giving birth in major tertiary hospitals and women attended by specialist obstetricians [34], and there is a particular concern with the high rate of elective caesarean section where there is no medical indication, and a recommendation that there should be national leadership to reduce caesarean section rates [34]. It is timely that an RCT be undertaken to test the safety of the caseload model and to ascertain the effect of caseload midwifery on the rate of caesarean section births.

There is increasing evidence that a caesarean section has implications for subsequent pregnancies, including increased risk of placenta accreta and percreta [35]; decreased fertility [36-40]; and an increased risk of ectopic pregnancy and spontaneous abortion [41]. Evidence around the protective effect (or otherwise) of caesarean section on urinary and faecal incontinence is inconsistent and likely to be multifactorial. There is some evidence of increased neonatal respiratory morbidity for babies born by caesarean section [42,43], however the frequency of significant fetal injury may be greater with vaginal delivery [44]. There are also significant resource implications: the increasing caesarean section rate adds an economic burden to already under-resourced medical systems [45].

Significant questions remain regarding the safety and efficacy of the caseload model, as well as its sustainability, the impact on the workforce, and costs of the model, given how different caseload is to a model using a team of midwives. There have been few economic evaluations of midwifery models of care. Published studies have reported conflicting results: some have reported continuity of care to be more expensive [46] and others that continuity models are more cost effective [14,47], although the studies used different methods to calculate costs.

It is not clear whether continuity of carer per se is more important to women than consistent and personalised care, even if it is provided by a number of care-givers [26,48].

We plan to implement a caseload midwifery model under RCT conditions to evaluate its effect on the rate of caesarean section and on a range of significant secondary outcomes. This paper describes the trial protocol in detail.

## Methods/design

The study uses a two arm, unblinded randomised controlled design, stratified by parity, to compare caseload midwifery care with standard maternity care.

### Aims

This study aims to determine whether caseload (one to one) midwifery care for women at low risk of medical complications decreases the proportion of women delivering by caesarean section compared with women receiving 'standard' care. The primary hypothesis is that:

Women randomised to caseload midwifery care will have 5% fewer caesarean section births than women in standard care model, that is, 14% versus 19%.

Secondary aims of the study are to compare caseload midwifery and standard care with regard to differences in:

a) Maternal outcomes

- instrumental vaginal births, obstetric analgesia, perineal trauma, and induction of labour;

- postnatal depression;

- satisfaction with care;

- breastfeeding duration;

- smoking cessation.

b) Midwife outcomes (compared to midwives providing standard care)

- staff attrition from the model of care and the hospital;

- work satisfaction;

- burnout.

c) Costs and cost effectiveness

A final aim is to collect data on maternal and perinatal morbidity and mortality for inclusion in meta-analyses (the sample size will be insufficient to determine statistical differences). These include measures of perinatal morbidity and mortality and maternal mortality and morbidity.

Comprehensive process evaluation will be undertaken to explore sustainability issues and to assess intervention compliance.

### Outcome variables

#### Primary outcome

The principal outcome of the study is the proportion of women having a caesarean section birth.

For the secondary aims of the study the following variables will be collected:

a) Instrumental vaginal births

b) Obstetric analgesia

c) Perineal trauma

d) Induction of labour and augmentation of labour

e) Satisfaction with care

f) Proportion of women breastfeeding to two and six months

g) Postnatal depression

h) Smoking

i) Costs

j) Staff attrition and satisfaction

#### Other related outcomes

measures of perinatal morbidity and mortality (e.g. fetal or neonatal death, intraventricular haemorrhage, necrotising enterocolitis, sepsis, severe respiratory distress syndrome, special care nursery admissions; Apgar scores, seizures); and maternal morbidity and mortality (e.g. postpartum haemorrhage, eclampsia, postpartum pyrexia, pulmonary embolus).

### Study population

Women attending for a booking visit at the antenatal clinic of a tertiary maternity hospital in Melbourne, Australia during the recruitment period and who are identified as being at low medical risk will be approached to participate in the trial.

#### Inclusion criteria

- English-speaking: able to speak, read and write in English;

- Less than 24 completed weeks gestation at recruitment;

- Low-medical risk at recruitment (list below);

- Singleton pregnancy.

#### Exclusion criteria

- Planned, elective caesarean section

- Considered to be at increased medical or obstetric risk according to the following criteria:

#### Medical criteria

○ Age > 42 years (subject to medical review)

○ Alcohol or drug abuse

○ History of anaesthetic difficulties (subject to medical review)

○ Anaemia (< 90 g/l not responding to treatment)

○ Asthma and/or chronic bronchitis (poorly controlled or requiring hospitalisation in the last 12 months)

○ Autoimmune diseases (includes antiphospholipid antibodies)

○ Bleeding disorders and/or haemolytic disease

○ Body mass index ≥ 35 or < 17

○ Cardiac disease

○ Diabetes mellitus

○ Endocrine disorders

○ Epilepsy requiring anticonvulsants in the previous twelve months

○ Gastrointestinal disorders (subject to medical review)

○ Haemoglobinopathy (major)

○ HIV positive status

○ Hypertension

○ Infectious disease (e.g. Acute Hepatitis C)

○ Neurological disorders

○ Severe psychiatric illness (subject to psychiatric advice)

○ Physical disability (e.g. paraplegia)

○ Renal disease

○ Respiratory disease (chronic/disabling)

○ Thromboembolic disease

○ Thyroid disease (uncontrolled)

#### Obstetric/gynaecological criteria

○ Birthweight of previous baby < 2500 g or > 4500 g (subject to medical review)

○ Significant cervical conditions (e.g. previous cone biopsy)

○ Fetal abnormality requiring specialised neonatal care

○ Previous mid trimester loss (× 2)

○ Multiple pregnancy

○ Parity ≥ 5 (subject to medical review)

○ Placental abruption (previous significant)

○ Previous significant postpartum haemorrhage (subject to medical review)

○ Pre-eclampsia (previous)

○ Puerperal psychosis (previous)

○ Recurrent miscarriage (× 3)

○ Rhesus isoimmunisation or other significant blood group antibodies

○ Previous stillbirth (not due to congenital malformation)

○ Uterine surgery (e.g. previous caesarean section)

○ Uterine myoma or malformation (subject to medical review)

### Sample size

Initial power calculations were based on the caesarean section rate for women who were low risk at booking at the Royal Women's hospital in 2005, i.e. 19%. It was hypothesised that the caseload model of care would decrease the caesarean section rate from 19% to 14%. In order to detect such a difference (with 80% power and 95% confidence) we needed 904 women in each trial arm. Allowing for 10% loss to follow up, 1004 women in each group were required, i.e. a total sample of 2008. This sample size also enables the detection of a range of other statistically significant differences to be detected for the major secondary outcomes, as shown in Table 1.

**Table 1 T1:** Power calculations with n = 904** in each arm

*Outcome*	*Standard care*	*Caseload*	*Power to detect specified difference*
	%	%	
Birth by caesarean section	19	14	80
Instrumental vaginal birth	10.6	6.6	84
Epidural analgesia	18	13	82
Intact perineum or unsutured laceration (increase)*	41.2	48.2	84
Intact perineum or unsutured laceration (decrease)*	41.2	34.2	86
3rd or 4th degree laceration* (would not miss this difference)	1.7	3.4	57
Induction of labour	27	21	84
Augmentation of labour	19	14	80
Exclusive breastfeeding at 6 months	8	12	79
Any breastfeeding at 6 months	53	63	99
Postnatal depression at 8 weeks	15	10	88
Postnatal depression at 6 months	15	10	88
Smoking at time of birth	15	10	88

*These estimations exclude caesarean births

** Allows for loss to follow-up

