### Data analysis

#### Quantitative analysis

This will be undertaken using STATA [51] and data will be collected to meet the CONSORT guidelines for reporting of randomised trials.

The first stage of analysis will check the comparability of participants allocated to the two groups. The intervention group will be compared with the standard care group by intention to treat analysis. Proportions of women having a caesarean section will be compared using chi-square tests and odds/risk ratios. Comparison of means will be undertaken for continuous variables using t-tests where data are normally distributed or medians compared using Mann-Whitney U tests otherwise. Ranked or Likert-type scales will be analysed using cumulative odds ratios. Where there are differences in baseline characteristics of the women in the two groups which might be associated with outcomes, an additional multivariate analysis will be carried out.

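### Table 1 says the trial would not miss a doubling of 3rd/4th degree laceration, yet the same row gives 57% power, and that figure does not apply the footnoted exclusion of caesarean births to the sample size

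*Protocol article*

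**What the plan says.** All the statements at issue stand in the Sample size section of the protocol article.

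- The primary calculation is for caesarean section, 19% against 14%: "with 80% power and 95% confidence) we needed 904 women in each trial arm". Loss is then added: "Allowing for 10% loss to follow up, 1004 women in each group were required".
- The text introduces Table 1 as follows: "This sample size also enables the detection of a range of other statistically significant differences to be detected for the major secondary outcomes".
- The table is headed "Power calculations with n = 904 in each arm", with a note that this number already allows for loss to follow-up.
- The severe-laceration row is labelled "3rd or 4th degree laceration* (would not miss this difference") and gives 1.7 for standard care (%), 3.4 for caseload (%) and 57 for power (%). It is the lowest power in the table; the other rows run from 79 to 99.
- The asterisk marks this row and the two intact-perineum rows: "These estimations exclude caesarean births".

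The Aims section lists perineal trauma among the secondary maternal outcomes. Its caveat that the sample is too small for statistical comparison concerns a separate group, maternal and perinatal morbidity and mortality collected for meta-analysis. Nothing in the article withdraws or qualifies the label on the laceration row.

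**The concern.** A power of 57% and a promise not to miss the difference cannot both stand. The row specifies a worse outcome under the new model of care, and the Background gives testing the safety of that model as a purpose of the trial. A reader who relies on the label could take a non-significant comparison as evidence against a doubling of severe perineal injury, when such a result would be common even if the doubling were real.

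A second problem lies beneath the first. The footnote restricts the starred rows to vaginal births, but the heading gives the full 904 per arm. If the restriction was not carried into the sample size, the printed power is itself too high, and the two intact-perineum rows are affected in the same way.

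**Working it through.** **Inputs.** From Table 1: p1 = 0.017, p2 = 0.034, n = 904 per arm. From the Sample size text: 95% confidence (alpha 0.05), caesarean rates 19% and 14%, 10% loss, 1004 randomised per arm. Sidedness is not stated. Two-sided is assumed because chi-square tests are planned (Quantitative analysis: "Proportions of women having a caesarean section will be compared using chi-square tests and odds/risk ratios") and because it reproduces the table.

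**Formula.** Normal approximation for two proportions:

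power = Φ[(|p2 − p1| − c − 1.96·s0) / s1]

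where s0 = √[p̄(1 − p̄)(1/n1 + 1/n2)], s1 = √[p1(1 − p1)/n1 + p2(1 − p2)/n2], p̄ is the pooled proportion, and c = ½(1/n1 + 1/n2) with continuity correction or 0 without.

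**Step 1: reproduce the plan's figure.** At 904 per arm, c = 0.001106, s0 = 0.007415 and s1 = 0.007404.

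- Corrected: (0.017 − 0.001106 − 0.014532)/0.007404 = 0.184, so power is 57.3%. The table states 57.
- Uncorrected: (0.017 − 0.014532)/0.007404 = 0.333, so power is 63.1%.

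The corrected method also gives exactly 904 per arm for 19% against 14% (864 without correction) and matches every other row of Table 1 within one point. It is therefore taken as the table's method. Taken alone, 57 could also come from an uncorrected calculation on 777 per arm (56.6%), but that method does not give 904 for the primary outcome, and it gives 79.3 and 81.3 for the intact-perineum rows, where the table has 84 and 86.

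**Step 2: apply the footnote.** Vaginal births: 904 × 0.81 = 732 and 904 × 0.86 = 777. Then c = 0.001327, s0 = 0.008159 and s1 = 0.008068.

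- Corrected: (0.017 − 0.001327 − 0.015991)/0.008068 = −0.039, so power is 48.4%.
- Uncorrected: (0.017 − 0.015991)/0.008068 = 0.125, so power is 55.0%.

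**Step 3: drop the loss to follow-up.** 1004 × 0.81 = 813 and 1004 × 0.86 = 863. Power is 53.3% corrected and 59.4% uncorrected.

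| Births per arm (standard, caseload) | Power, corrected | Power, uncorrected | Rise from 1.7% detectable at 80% power (corrected / uncorrected) |
|---|---|---|---|
| 904, 904 (as printed) | 57.3% | 63.1% | to 4.0% / 3.9% |
| 732, 777 (vaginal births, 10% loss) | 48.4% | 55.0% | to 4.3% / 4.1% |
| 813, 863 (vaginal births, no loss) | 53.3% | 59.4% | to 4.1% / 4.0% |

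A one-sided test at 0.05 on all 904 per arm would give 69.1% corrected or 74.2% uncorrected. To reach 80% power for 1.7% against 3.4% (two-sided) takes 1464 vaginal births per arm with correction, or 1349 without.

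**Step 4: the other starred rows, by the table's method.**

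| Intact perineum or unsutured laceration | Stated | 904 per arm | 732, 777 | 813, 863 |
|---|---|---|---|---|
| 41.2% to 48.2% | 84 | 83.9 | 76.5 | 80.9 |
| 41.2% to 34.2% | 86 | 85.7 | 78.6 | 82.8 |

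The footnoted exclusion was thus not applied to n in any of the three rows. It may have been applied to the assumed rates only.

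**The case against.** The strongest defence is that the 57 is printed in the same row under a column headed as power, so the limitation is disclosed, and that the label may be a slip for a difference the investigators would not want to miss. The disclosure is real and limits the seriousness of the point. The slip is plausible, but the text does not say so, and the introductory sentence supports the literal reading. Either way the words need changing.

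The exact replacement figure is also open to challenge, and that objection stands. The 48% depends on the continuity correction, on caesarean rates exactly as hypothesised and on the full 10% loss. Lacerations are taken from the medical record, and the protocol aims to obtain data on women who seek care elsewhere, so loss may be smaller for this outcome. The range on vaginal births is about 48% to 59%, and the printed 57 lies inside it. A reader might infer that 48% is the single true power; the documents do not settle that.

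Two further inferences go too far. A reader might conclude that the trial will report a non-significant result as ruling out a doubling. No section sets such a rule, so the text supports only that a result could be read that way. A reader might also take this as the only row pointing towards harm. The intact-perineum row with a decrease from 41.2% to 34.2% is adverse too. The laceration row is distinctive only in carrying the label.

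**Conclusion.** The point holds. On the document's own figure, a true rise from 1.7% to 3.4% would be missed 43% of the time. With caesarean births excluded as the footnote states, it would be missed 45% to 52% of the time with 10% loss, and 41% to 47% with none. These figures assume a two-sided 0.05 test and caesarean rates of 19% and 14%. No variant examined, including a one-sided test on all 904 per arm, reaches 80%.

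The error lies in what the table claims. The primary outcome, the planned sample size and the planned analysis are untouched. The size of the correction to the starred rows depends on how much loss applies to outcomes taken from records, so the assumptions should be printed with the figures.

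**What to change.** 1. Delete the parenthetical label, or reword it so that it no longer claims the difference will be found.
2. Recompute all three starred rows on vaginal births by the table's own method and state the assumptions (caesarean rates, loss, continuity correction, sidedness). With 10% loss this gives about 48% for severe laceration, and 76.5% and 78.6% in place of 84% and 86% for intact perineum. Correcting the laceration row alone would leave the table on mixed denominators.
3. Add that 80% power for severe laceration is reached only for a rise from 1.7% to about 4.0% to 4.3%, depending on loss and on the continuity correction.
4. Except severe laceration from the introductory sentence on detectable differences, so that a non-significant result could not be taken as excluding a doubling.

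The cost is a label, three table entries, a note on assumptions and one sentence. The stated figures become less favourable. Design and sample size do not change.

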### Study participation

#### Baseline

After consenting to participate in the study and prior to randomisation, women will be asked to complete a baseline questionnaire, which includes demographic data.

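### The aim is smoking cessation, but the powered outcome is smoking prevalence at birth in all women, which measures cessation only indirectly and makes no routine use of baseline smoking

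*Protocol article*

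**What the plan says.** Under Aims, the maternal outcomes to be compared include "smoking cessation". The list under Outcome variables shortens this to smoking, with no denominator, time point or definition.

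Table 1, under Sample size, has one row on the subject, "Smoking at time of birth": 15% in standard care, 10% in caseload care, power 88%, on the common 904 per arm. Rows with a restricted denominator are marked; the perineal rows carry the footnote "These estimations exclude caesarean births". The smoking row has no mark, so it refers to all women.

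Before randomisation, "women will be asked to complete a baseline questionnaire, which includes demographic data". The article does not say whether smoking is asked. Randomisation is stratified by parity only.

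Under Quantitative analysis, groups are compared by intention to treat. An additional multivariate analysis follows "Where there are differences in baseline characteristics of the women in the two groups which might be associated with outcomes".

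**The concern.** Cessation is a change from a starting state. Prevalence at birth combines how many women smoked at recruitment, how many of them stopped, and how many others relapsed or started. A woman who never smoked counts the same as one who quit. The stated aim and the powered outcome are therefore different quantities, and a 5-point difference in prevalence cannot be read as a quit rate.

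Baseline smoking is also likely to be the strongest predictor of smoking at birth. Under the stated rule it is used only once an imbalance has been noticed, and then only in an additional analysis. Precision is left unused, and whether to adjust depends on the data. At stake is the chance of missing a real but smaller effect on smoking, and a result that does not answer the question under Aims.

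**Working it through.** **Inputs from the article.** 904 analysed women per arm; 15% against 10% smoking at birth; stated power 88%; 95% confidence, read as two-sided alpha 0.05.

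**Assumptions, because the article gives no figure.** Baseline smoking prevalence b is taken as 20% to 40%, and no woman who is a non-smoker at recruitment smokes at birth. The second assumption is relaxed in step 4.

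**1. The stated figure.** Continuity-corrected power for two proportions, with p̄ the mean of p1 and p2:

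power = Φ{ [ |p1 − p2| − 1/n − 1.96·√(2p̄(1 − p̄)/n) ] / √( [p1(1 − p1) + p2(1 − p2)]/n ) }

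With n = 904, p1 = 0.15, p2 = 0.10: (0.05 − 0.0011 − 0.0305)/0.0155 = 1.187, and Φ(1.187) = 88.2%. This matches Table 1. Without the correction the result is 89.6%. The corrected method also gives 904 per arm for 19% against 14%, so it appears to be the one the trial used.

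**2. The same effect among baseline smokers.** Here n = 904·b per arm, and the proportions still smoking at birth are 0.15/b and 0.10/b. At half the effect the second proportion is 0.125/b.

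| b | Baseline smokers per arm | Quit rates, 15% vs 10% | Power, 15% vs 10% | Power, 15% vs 12.5% |
|---|---|---|---|---|
| All women (Table 1 comparison) | 904 analysed | none available | 88.2% | 31.4% |
| 20% | 181 | 25% vs 50% | 99.8% | 69.0% |
| 25% | 226 | 40% vs 60% | 98.8% | 53.3% |
| 30% | 271 | 50% vs 67% | 97.2% | 46.1% |
| 40% | 362 | 62.5% vs 75% | 94.5% | 39.4% |

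At b = 20%, full effect: (0.25 − 0.0055 − 0.0998)/0.0492 = 2.94, and Φ(2.94) = 99.8%. Carried on to b = 50%, the two powers are 92.6% and 36.3%. The gain shrinks as b rises but stays positive.

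**3. Detectable difference.** At 88% power and a 15% control rate, the all-women difference that can be detected falls from 5 points to 3.2 (15% to 11.8%) at b = 20%, and to 4.1 (15% to 10.89%) at b = 30%.

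**4. Some smoking at birth among baseline non-smokers.** In simulation, 1% to 2% of baseline non-smokers smoked at birth and the all-women rates were held at 15% and 10%. A Mantel-Haenszel test on all women, stratified by baseline smoking, had power 98.7–99.4% at b = 20%, 97.3–98.1% at b = 25% and 93.5–94.5% at b = 40%. The unstratified test, without continuity correction, had about 90%. The gain therefore does not require dropping the non-smokers.

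**5. Chance imbalance.** Imbalance in baseline smoking reaches the outcome only through the share still smoking at birth. Its contribution to the difference has

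SD = √{ [(0.15/b)² + (0.10/b)²]·b(1 − b)/904 }

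At b = 20%: √(0.8125 × 0.16/904) = 1.2 points. At b = 40%: √(0.2031 × 0.24/904) = 0.7 points. The total standard error of the 15% against 10% comparison is √(0.2175/904) = 1.55 points and already contains this part.

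**The case against.** The strongest reply is that the all-women contrast is a sound intention-to-treat comparison with adequate and correctly calculated power. With little uptake, a difference in smoking at birth arises mainly from quitting. All of that stands. A reader might infer that the outcome does not measure cessation at all; the article does not support that, because the outcome measures cessation indirectly.

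A reader might also infer that much of the available power is lost. At the planned effect the gain cannot exceed 12 points, since power is already 88%. Its size depends on a baseline prevalence that the article does not give, and it is modest when that prevalence is high.

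Nor does chance imbalance in baseline smoking pass whole into the result or create extra false positives. The raw SD of the imbalance, √(2b(1 − b)/904), is 1.9 points at b = 20%, which is more than the 1.55-point standard error of the whole comparison. Only the part in step 5 carries through, and it is already inside the 5% type I error.

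Restricting to baseline smokers has its own cost. Entry is allowed up to 24 weeks, so a woman who stopped earlier in pregnancy counts as a non-smoker at recruitment and may relapse by birth. Restriction misses that and all-women prevalence keeps it, so the two analyses are not interchangeable.

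Finally, definitions for a secondary outcome often sit in an analysis plan, and none is shown here. That excuses missing detail. It does not excuse an aim and a powered outcome that differ within the article, or an adjustment rule that the article itself makes conditional on observed differences.

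**Conclusion.** The concern holds in a limited form. The aim is cessation, the powered outcome is prevalence at birth in all women, and baseline smoking is used at most conditionally. The comparison is valid and its 88% is right, but it gives no quit rate and is less precise than it could be.

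For assumed baseline smoking of 20% to 40% and no new starters, power among baseline smokers is about 99.8% to 94.5% against 88% at the planned effect, and about 69% to 39% against 31% at half of it. The direction is the same at every prevalence tested; the size rests on the assumed prevalence. Chance imbalance contributes an SD of about 0.7 to 1.2 points at the planned effect, which is a matter of precision and not of type I error. The primary outcome and its sample size are not affected. The change is worth making because it is cheap and improves on the stated rule.

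**What to change.** - Adjust the all-women model for smoking at birth for smoking status reported before randomisation, whether or not an imbalance is seen.
- Also report cessation, defined as not smoking at birth among women who smoked at recruitment, as the estimate that answers the stated aim. Keep the all-women result beside it, since the cessation estimate does not capture relapse among women who stopped before recruitment.
- Confirm that the pre-randomisation questionnaire asks about current smoking, and add the item if it does not. This should be done before or early in recruitment, because baseline status cannot be reliably recovered after randomisation.

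The cost is a change of analysis wording and at most one question in a form that women already complete. The drawback is the smaller denominator for the cessation estimate: about 181 to 362 women per arm under the assumed 20% to 40%.
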